### Sample size calculation

2.1

The sample size was calculated (G∗ Power software version 3.1.9.2, Kiel, Germany) by *t* test for paired groups, since we have 2 groups (G1 conventional PS and G2 oral use PS). The effect size was determined using the formula: 

We select the worst scenario, that is, the largest standard deviation between means. The mean values of control and treated groups, as well as the standard deviation were taken from 1 study.^[18]^ The error was set at 5% and the power test at 95%. This value was calculated to provide 95% strength (α = 0.05). According to the calculus, a ample of 64 patients will be necessary to detect differences in *Tannerella forsythia* level.^[18]^ Other factors related to secondary outcomes will be analyzed statistically.

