**Method::**

In this randomized, controlled, double-blind clinical bioequivalence protocol, 64 healthy patients with pericoronitis will be evaluated. Patients will be randomized into the positive control group (G1) (n = 32): irrigation with sterile saline and PDT (conventional MB at 0.005% concentration and irradiation with low intensity laser λ = 660 nm, 9J per point and radiant exposure of 318 J/cm^2^), and the experimental group (G2) (n = 32): treatment identical to G1, however, MB will be delivered in a new formulation for oral use. Microbiological analysis will be performed by RT-PCR for the bacterium *Tannerella forsythia.* Gingival crevicular fluid and saliva will be collected to evaluate cytokines by Luminex assay (Luminex Corporation, Austin, TX). The pain (visual analogue scale), swelling and buccal opening (digital caliper), and OHRQoL will also be evaluated through the OHIP-14 questionnaire. The variables will be evaluated in T1 (baseline), T2 (immediately after PDT), and T3 (4th day after PDT). Registration: clinicaltrials.gov NCT 03576105. Registered in July 2018.

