### Design

2.4

This is a controlled, randomized, double-blind, clinical trial:

G1—(positive control group) 32 patients with pericoronitis, irrigated with sterile saline and the PDT performed with conventional MB. The irradiation will be performed with low intensity laser λ = 660 nm, 9J per point and radiant exposure of 318 J/cm^2^.G2—(experimental group) 32 patients with pericoronitis treatment identical to G1, however the PDT will be delivered in a new formulation for oral use (patent application INPI BR1020170253902).^[19]^

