### Statistical analysis

2.7

The data will be collected, tabulated on Excel table developed for research and presented in a descriptive way. All statistics will be conducted using the SPSS 21 program package (SPSS Inc, Chicago, IL). In the first part of the results will be performed the descriptive analysis. Measures of: absolute number, mean, standard deviation, minimum value and maximum value, percentage and cumulative percentage will be used. The bacterial count will be normalized by conversion into logarithmic values will be compared by the student *t* test. In the second part, we will verify the inferential analysis for the numerical variables. Tests of Normality Skewness and Kurtosis will be used, then verification of the homogeneity of the variables. The ANOVA will be applied for repeated data, and the Spearman correlation, and the Huynh-Feldt, Greenhouse-Geisser, Box's conservative tests. If there is no normality of the sample will be used The Wilcoxon test will be used in order to compare before and after the PDT. The *P* value is set at *P* < .05 (95% level of significance). By the end of the study, randomized groups will be revealed and statistical analysis will be performed as group A or B. The meaning of A or B will be known after statistical analysis. The data will be evaluated by comparing 2 groups: experimental and control groups (gold standard).

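### The sample size rests on a paired t test, but the arms are independent groups of 32, so the stated 95% power is not supported by the calculation described

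*Protocol article*

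**What the plan says.** Protocol article, section 2.1 (Sample size calculation), says that G*Power was used with a t "test for paired groups, since we have 2 groups (G1 conventional PS and G2 oral use PS"). On the inputs it says: "The mean values of control and treated groups, as well as the standard deviation were taken from 1 study", and "We select the worst scenario, that is, the largest standard deviation between means". On the error rates: "The error was set at 5% and the power test at 95" percent. Whether the test is one- or two-sided is not stated. The result is given as "a ample of 64 patients will be necessary to detect differences in" the level of *T. forsythia*, which section 2.6 names as the primary outcome.

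The design is described elsewhere. The abstract (Method) has: "Patients will be randomized into the positive control group (G1) (n = 32"), with the same number in G2. Section 2.4 (Design) describes G2 as "32 patients with pericoronitis treatment identical to G1, however the PDT will be delivered in a new formulation for oral use". Section 2.7 (Statistical analysis) says: "The data will be evaluated by comparing 2 groups: experimental and control groups (gold standard").

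**The concern.** A paired t test is for two measurements on the same unit or on matched units. Its sample size counts pairs, and its effect size is the mean difference divided by the SD of within-pair differences. Here each patient is randomised to one formulation, and the two arms hold different people. Having two groups is a reason for a two-sample test; section 2.1 gives it as the reason for a paired one.

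The 95% power is the only quantitative justification given for 64 patients. Both arms receive active photodynamic therapy and differ only in the methylene blue formulation, and the article calls the trial a bioequivalence study. A non-significant result could easily be read as showing that the formulations perform alike, and a reader would lean on the 95% figure in doing so. That figure should come from a calculation that fits the comparison.

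**Working it through.** **1. Is there any pairing between the arms?** The abstract and section 2.4 give two arms of 32, and section 2 gives 64 patients in total, so each patient contributes to one arm. No section describes a crossover, split-mouth or matched design. Section 2.3 mentions blocking in pairs of numbers, but this concerns how the 1:1 allocation list is built, not matching of patients. Section 2.7 compares the two arms. The between-arm observations are independent.

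**2. Can the plan's figure be reproduced?** Not directly. The effect-size formula, means and SD cannot be read in the text at hand, and this is not held against the plan. What can be done is to solve backwards for the standardised effect that would yield the stated size, then see what that effect implies for 32 against 32.

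Inputs from section 2.1: α = 0.05, power 0.95, N = 64. From section 2.4: 32 per arm. Assumed: two-sided test (one-sided variants are in step 6).

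**3. Back-solving the paired calculation** (noncentral t). With n pairs, df = n − 1 and noncentrality = dz·√n.
- If 64 is the number of pairs: df = 63, critical t = 1.998; 95% power needs noncentrality 3.661, so dz = 3.661/√64 = 0.458.
- If 64 patients means 32 pairs: df = 31, critical t = 2.040; 95% power needs noncentrality 3.722, so dz = 3.722/√32 = 0.658.

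**4. Power of the actual design.** For 32 against 32 independent patients, df = 62, critical t = 1.999, noncentrality = d·√(32/2) = 4d.

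Carrying the same standardised value over unchanged (d = dz):
- d = 0.458: noncentrality 1.83, power 44%; 95% power would take 126 per arm.
- d = 0.658: noncentrality 2.63, power 74%; 95% power would take 61 per arm.

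**5. Allowing for a pairing correlation.** If dz was built from a between-group SD and an assumed correlation ρ, then d = dz·√(2(1 − ρ)). Carrying dz over unchanged is the case ρ = 0.5. No correlation is given in the article; the range 0 to 0.75 is an assumption.

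| Branch | ρ = 0.75 | ρ = 0.5 | ρ = 0 |
|---|---|---|---|
| 64 pairs, dz = 0.458 | d = 0.324, power 25% | d = 0.458, power 44% | d = 0.647, power 72% |
| 32 pairs, dz = 0.658 | d = 0.465, power 45% | d = 0.658, power 74% | d = 0.931, power 96% |

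**6. One-sided variants, d = dz.** 64 pairs: dz = 0.416, power 50%. 32 pairs: dz = 0.595, power 76%. Sidedness alone does not restore 95%.

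**7. What 32 per arm deliver whatever was run.** Solving the independent test at n = 32 per arm, two-sided 5%: 95% power at d = 0.916, 80% power at d = 0.711. One-sided, 95% power is reached at d = 0.832.

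**The case against.** The strongest reply is that this is a misnamed independent test. The stated reason (two groups) is the reason for a two-sample test. The stated inputs, means of control and treated groups with the larger SD taken as the worst case, are two-sample inputs; neither a correlation nor an SD of differences is mentioned. An independent test at d of about 0.92 gives exactly 32 per arm at 95% power. This reading is open: the article does not prove it and does not exclude it. If it is right, the error is one of wording and the power figure stands.

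A second reply is that the paired test was meant for change within a patient from T1 to T3. The text does not fit this, since it names G1 and G2 as the two groups. Even if it did, that calculation would power a within-arm change, not the comparison of formulations.

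A third reply is that the amount of lost power depends on inputs that are not visible. That is correct and limits the claim. A reader might infer that the trial has only about half the power stated. The documents do not support that: 44% is one scenario (64 pairs, value carried over unchanged), the full range across both branches is about 25% to 96%, and the top of it includes the planned 95%.

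**Conclusion.** The contradiction between the paired test in section 2.1 and the parallel-group design is certain and does not depend on the missing effect size. The 95% power for 64 patients is therefore unsupported by the calculation as described.

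A loss of power is possible but not shown. It rests on whether a paired test was really run, whether 64 counted pairs or patients, and which correlation, if any, was entered. Power stays near 95% in two of the cases considered: 32 pairs with zero correlation, or an independent test at about 0.92 SD labelled as paired. In the other scenarios it is lower, in several of them well under 80%. The detectable differences for 32 per arm (step 7) depend only on the arm size, the 5% level, the sidedness and the usual t-test assumptions, with every patient analysed.

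**What to change.** First establish from the saved G*Power run which test was selected and whether its output was 64 in total, 64 pairs or 32 pairs. Then:

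- If an independent test was run, correct the label in section 2.1 to a t test for two independent means; the 95% stands with the effect size used.
- If a paired test was run, redo the calculation for two independent means on the log *T. forsythia* scale. Changing the label alone would misdescribe what was done.
- In either case, state the sidedness and what 32 per arm can detect: 95% power for a between-arm difference of about 0.92 SD (0.83 SD one-sided), or 80% for about 0.71 SD two-sided. If the difference the trial is meant to detect is smaller, give the lower power that results.

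The cost is one rerun and a few reworded sentences. Depending on what was run, the stated power may become less favourable or stay as it is. No change in enrolment, design or treatment is needed.

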The composition of this fluid resembles that of serum, and the intensity of its flow has been shown to vary as a function of gingival inflammation. There is a wide variation in the methods of collection, storage, and analysis along with elusion protocols making the values alter based on this variation.^[54]^ Kinney et al^[23]^ concluded that the greatest degree of sensitivity was noted with GCF biomarkers compared to saliva biomarkers on the identification of periodontal disease progression, reason why it will be used this method in this study, and it will be compared to salivary cytokines.

MB was chosen as a PS. MB absorbs well the red light^[14]^ and it is the most commonly used PS in dentistry for antimicrobial action.^[6]^ The 3 minutes pre-irradiation time of MB was established based on Joseph et al^[12]^ research. Any decrease of penetration of MB in biofilm may be attributed to a reduced action of PDT,^[16]^ thus an adequate pre-irradiation time is desirable.

It is difficult to predict the efficacy of PS as many factors may contribute to their cellular photoactivity, which is usually related to properties of their monomers species.^[39]^ A decrease in photochemical effects may occur due to dimerization of MB.^[6]^ MB has a tendency to aggregate, also called metachromacy, which is the property of forming dimer or higher aggregation products upon increasing dye concentration or changing the microenvironment (e.g., high ionic strength). It interacts with the anionic macromolecule lipopolysaccharide resulting in the generation of MB dimmers.^[16]^ The absorption spectrum of MB is changed upon aggregation, altering the wavelength of highest absorption to lower wavelengths.^[11]^ Bergmann and Konski^[55]^ showed that the absorption spectrum of monomer and dimer are different. Monomer absorbs light at the wavelength of 660 nm and the dimer at 590 nm. Besides, depending on its ground state monomer/dimmer equilibrium the photochemical properties which can be shifted from type II to type I.^[10,56]^ This fact can interfere with the antimicrobial potential of PDT, since it decreases the formation of singlet oxygen.^[57]^ Here, by changing the MB vehicle, the study aims to verify if the reduced aggregation improves the antimicrobial effect.

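### The 95% power in section 2.1 is unsupported for G1 versus G2: it rests on a difference between the control and treated groups of another study and on a paired t test, whereas the trial compares two independent arms that both receive PDT

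*Protocol article*

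**What the plan says.** Protocol article, section 2.1 (Sample size calculation), sets alpha and power together: "The error was set at 5% and the power test at 95" per cent. The calculation used a t "test for paired groups, since we have 2 groups (G1 conventional PS and G2 oral use PS"). Both the difference and its spread are borrowed: "The mean values of control and treated groups, as well as the standard deviation were taken from 1 study" (ref. 18). For the spread, the article adds: "We select the worst scenario, that is, the largest standard deviation between means". The result is 64 patients for *T. forsythia* level. The text does not say what the two groups of ref. 18 received, and it gives no means, SD or effect size.

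Section 2.4 (Design) describes G1 as a positive control that receives saline irrigation and PDT with conventional methylene blue. G2 is "32 patients with pericoronitis treatment identical to G1, however the PDT will be delivered in a new formulation for oral use". Section 2.5 gives both arms the same irrigation volume, dye volume, dye concentration and laser settings. The Discussion states the question: "by changing the MB vehicle, the study aims to verify if the reduced aggregation improves the antimicrobial effect".

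**The concern.** A power statement holds for one contrast, one test and one assumed difference. On two of these, section 2.1 does not match the trial.

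- **The difference.** It comes from a control and a treated group in another study. Here the contrast is one vehicle against another, with PDT in both arms. Nothing in the article links the two. The sizing study is ref. 18, while the new formulation is referenced separately to a patent application (ref. 19).
- **The test.** G1 and G2 are different patients allocated 1:1 (section 2.3). They are not pairs, so a paired calculation does not describe their comparison.

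Taking the largest SD is cautious about the denominator of the effect size. It does nothing for a numerator whose relevance has not been shown.

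At stake is how the primary result is read. If real power is well below 95%, a non-significant result is likely even when the new vehicle is better. The abstract and the opening of the Methods call this a bioequivalence study, and section 2.7 calls the control the gold standard. In that setting a reader who trusts the 95% could mistake a null result for equivalence.

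**Working it through.** **Inputs.** From the article: alpha 0.05 and power 0.95 (section 2.1); 64 patients, 32 per arm (sections 2.1 and 2.4); 1:1 allocation (section 2.3). Not available: the means, the SD and the effect size. The effect-size formula was lost when the text was extracted, and that is not counted against the plan. Sidedness is not stated, so two-sided is assumed.

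**Reproducing 64.** This is not possible without an effect size. What can be done is to solve backwards for the standardised effect at which each design has 95% power.

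**Formulas (noncentral t).**
- Independent arms, n per arm: noncentrality = d·√(n/2), df = 2n − 2. With n = 32 this is d·√16 = 4d, df = 62, two-sided critical value 1.999.
- Paired, n pairs: noncentrality = dz·√n, df = n − 1.

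**Step 1: the effect implied by 95% power.**

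| Design | Effect needed | Noncentrality |
|---|---|---|
| Independent, 32 per arm | d = 0.916 | 4 × 0.916 = 3.66 |
| Paired, 64 pairs | dz = 0.458 | 8 × 0.458 = 3.66 |
| Paired, 32 pairs | dz = 0.658 | 5.657 × 0.658 = 3.72 |

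One-sided values are 0.832, 0.416 and 0.595. For 80% power, independent arms of 32 need d = 0.711 (two-sided).

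**Step 2: if 64 came from an independent-groups calculation.** The borrowed effect would then be 0.916. The share of it that the formulation contrast would show is an assumption:

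| Share of borrowed effect | d | Power, 32 per arm | Per arm for 95% power |
|---|---|---|---|
| 100% | 0.916 | 95% | 32 |
| 75% | 0.687 | 77% | 57 |
| 50% | 0.458 | 44% | 125 |
| 25% | 0.229 | 15% | 498 |

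**Step 3: if 64 came from the paired test that the article names.** Suppose the standardised effect put into the paired test is also the between-arm d.
- 64 pairs: 4 × 0.458 = 1.83, power about 44%.
- 32 pairs: 4 × 0.658 = 2.63, power about 74%.

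This step depends on how the effect size was formed. In general d = dz·√(2(1 − r)), where r is the within-pair correlation, so reusing dz as d corresponds to r = 0.5. At r = 0 the factor is √2. For 32 pairs, d = 0.658 × 1.414 = 0.93, which is just above the 0.916 needed, so 95% would be met. For 64 pairs, d = 0.458 × 1.414 = 0.65, which is short even of the 0.71 needed for 80%. The article does not let a reader tell which case applies.

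**The case against.** The strongest reply is that ref. 18 is not at hand. The article itself uses the word control for an active PDT arm: G1 is a positive control in section 2.4, and section 2.7 contrasts experimental and control groups. The control and treated groups of ref. 18 could therefore both have had PDT. Section 2.1 also names G1 and G2 as the compared groups just before it describes its inputs. A condensed article may leave the justification to the full protocol. The shares in step 2 are chosen, and a similar table could be drawn up for any trial. The loss in step 3 comes from the paired test, not from the borrowed contrast.

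Much of this stands. A reader might infer that ref. 18 compared PDT with no PDT, that its difference must exceed the formulation effect, and that the 95% is therefore wrong. The document supports none of these steps: the borrowed difference could be larger than, equal to or smaller than the formulation effect. Nor does the article say that a non-significant result will be read as equivalence. The Discussion asks a superiority question.

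The objection does not rescue the power claim. The article does more than leave a detail out: it states a basis and a test and draws a 95% figure from them. The paired test contradicts the parallel-group design within the same document, whatever ref. 18 contains.

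**Conclusion.** The point holds in a limited form: the 95% power is not established for G1 versus G2. Two things support this. The borrowed difference is not shown to be one between methylene blue formulations, and the named test is for paired data while the arms are independent.

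The size of any shortfall is unknown. The figures of 15% to 77% (a smaller formulation effect) and of 44% or 74% (a paired effect size carried over) are illustrations under the stated assumptions, and under some assumptions 95% would still be reached. What can be stated firmly is what the design can detect: with 32 per arm, a two-sided 5% level and no loss of patients, about 0.92 SD at 95% power or 0.71 SD at 80% power.

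The trial can proceed as designed, but the power statement for its primary outcome should be corrected.

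**What to change.** Keep 64 patients and rewrite section 2.1:

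1. Describe the calculation as an independent two-group comparison (two-sided 5%) of log *T. forsythia* at T3, and drop the reference to paired groups.
2. Name the between-formulation difference considered important. If the SD, or the difference, is still taken from ref. 18, say what its groups received and why the figure applies here.
3. Replace the 95% power claim with what 32 per arm can detect: about 0.92 SD at 95% power or 0.71 SD at 80%. If the important difference is smaller than that, say so.
4. State that the between-group difference will be reported with its confidence interval and that a non-significant result will not be read as equivalence.

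The cost is rewording only, with no extra patients or procedures. The downside is a less favourable stated power.

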### Inclusion and exclusion criteria

2.2

Participants in this study will be evaluated to meet the eligibility criteria: ASA I patients (negative medical history), with age of 13 years old or over till 60 years, with lower third molar erupted or partially erupted, with pericoronitis. Patients should have at least one lower third molar partially visible in the oral cavity to be examined. All participants, regardless of age, gender, cultural level, or socioeconomic status may participate in the study. The following patients will be excluded: those allergic to MB, pregnant or breastfeeding women, with presence of purulent exudate, those who have used anti-inflammatory drugs or antibiotic medications for the last 3 months, those with fever (with temperature above 37.8°C), that may suggest an infection. The local temperature will be measured in the mandibular angle region 2 cm above the lower jaw board (Safety 1st model “No Touch Forehead,” Columbus, OH).

### Randomization

2.3

An external researcher who will not participate in this study will perform randomization through the Microsoft Excel program, version 2013 (Microsof, Redmont, WA). To decide the type of the PS, another researcher will randomize into 4 blocks with 16 patients blocking in pairs of numbers (1:1) designed as A or B. As the study will be performed in a double-blind manner, neither the patient nor the operator will know which MB will be used as PS. To randomly distribute the treatments, the same researcher (not involved in the study) will prepare the envelopes. The letters (A or B) drawn will be placed into opaque envelopes labeled with sequential numbers. The envelopes will be sealed and remain in the same numerical order in a safe place until PDT treatment. These data will only be revealed after statistical analysis.

### Design

2.4

This is a controlled, randomized, double-blind, clinical trial:

G1—(positive control group) 32 patients with pericoronitis, irrigated with sterile saline and the PDT performed with conventional MB. The irradiation will be performed with low intensity laser λ = 660 nm, 9J per point and radiant exposure of 318 J/cm^2^.G2—(experimental group) 32 patients with pericoronitis treatment identical to G1, however the PDT will be delivered in a new formulation for oral use (patent application INPI BR1020170253902).^[19]^

